### Data collection

#### Primary outcome

The primary outcome of this study is sleep quality of 0-2-year-old infants and will be assessed with a sleep diary filled out by parents, measuring the number and duration of daytime naps, bedtime, time to sleep onset, the number and duration of nighttime awakenings and the time the child gets out of bed in the morning. Parents are asked to fill in the diary for four consecutive days [62]. Sleep quality will be assessed when the infant is 10 weeks, 6 months, 9 months, 14 months and 24 months old. The sleep diary was developed for this study and can be filled in digitally or on paper. All study outcomes, assessment moments and instruments are listed in Fig. 2.

### Secondary outcomes

**Sleep Diary.** Bedtime regularity will be assessed using the bedtime item from the sleep diary. Parental perception of infant sleep quality will be measured with two closed-ended questions integrated in the sleep diary: ‘How well did your child sleep last night?’ and ‘How well did your child sleep today during the day?’ These questions are answered on a five-point Likert scale ranging from very well to very badly. Parental sleep is measured with the question: ‘How did you sleep last night?’ and can be answered on a five-point Likert scale ranging from very well to very badly. Parental behaviour regarding infant sleep management is assessed with two study-developed questions in the sleep diary. The first question focuses on how the parent put the child to bed that night and can be answered with one of the following three answers: ‘awake and not tired’, ‘awake and tired’ and ‘when my child was asleep’. The second questions asks how the child fell asleep that night, and can be answered with one of the following four answers: ‘on his/her own, without a parent in the room’, ‘with a parent present in the room, not attending the child in any way’, ‘with a parent present in the room, attending the child’ or ‘the child fell asleep during feeding’.

**Questionnaires.** The questionnaires of this study can be filled in digitally or on paper. Parental behaviour regarding infant sleep management is assessed with the use of the 11 parental behaviour items from the Brief Infant Sleep Questionnaire (BISQ-R): a validated questionnaire for measurement of infant sleep and related parental behaviours and perceptions [63, 64]. Parental perception of infant sleep and parental self-efficacy regarding infant sleep management are assessed using the three parent perception items and the self-efficacy item from the BISQ-R, respectively.

Parental knowledge of infant sleep will be assessed with three self-developed questions comprising of statements about infant sleep, below which the participant states on a four-point scale whether or not they believe the statement to be true. Knowledge themes examined are normal infant sleep patterns and the expected effects of using a bedtime routine, using a regular, structured day routine and putting the infant to bed at fixed moments. Parental knowledge is measured at 10 weeks, 6 months and 14 months. The knowledge themes at 14 months also include knowledge of behavioural sleep methods, such as controlled crying methods.

Parental beliefs on limit setting are measured with five limit setting items from the validated Maternal Cognitions about Infant Sleep Questionnaire (MCISQ) [65]. Parent’s perceived frequency of YHC professionals inquiring after their infant’s sleep will be investigated with a self-developed question that asks how often YHC professionals generally inquire after their infant’s sleep and can be answered on a five-point Likert scale ranging from always to never.

Parental satisfaction with YHC sleep advice is only investigated in parents that discussed sleep with a YHC professional and is assessed with a self-developed question on how parents perceive YHC sleep advice. The question can be answered on a five-point Likert scale ranging from very good to very bad. Lastly, the number of parents receiving help for infant sleep issues outside of YHC is assessed with a closed-ended question that explores whether parents received help from sources outside of YHC during the prior period. In case parents received help outside of YHC, they are asked to state who provided help.

To be suitable for this study, the used subscales from the BISQ-R and MCISQ were translated into Dutch and were adjusted to be suitable for parents with limited (health) literacy. This was done by three sleep health experts from Maastricht University (the Netherlands) who are also authors of this manuscript, together with an advisor on comprehensible communication and writing for people with limited (health) literacy. The experts are native Dutch speakers also proficient in English. Each expert independently translated the BISQ-R and MCISQ subscales into Dutch versions of these subscales. In a joint session, the three individually translated versions were discussed until consensus was reached on a preliminary Dutch version. Together with the communication advisor, the literacy level of the preliminary Dutch version was adjusted to be maximally B1 CEFR language level. This questionnaire was then translated back to English by another sleep health expert from Maastricht University who is a native English speaker and proficient in Dutch. The original BISQ-R and MCISQ items and the back-translated English versions were then compared on accuracy and clarity. Some final adjustments were made and consensus was reached on the final Dutch versions of the subscales from the BISQ-R and MCISQ.

### Demographic information

In a demographics questionnaire that has to be filled in before the infant is 14 weeks old, parents are asked to provide demographic information about themselves and their infant. Participant’s demographic information consists of their age and family composition and of the gender, ethnicity, educational level and employment status of participant and partner. Infant demographic information consists of infant’s age, gender at birth, birth order position, ethnicity and whether the infant primarily receives breastfeeding, formula feeding or a combination of the two.

### Process evaluation

A mixed method process evaluation will be conducted focusing on evaluation of program reach, adoption, implementation and maintenance and gaining insight in program working mechanisms [49]. The process evaluation will be conducted with parents and YHC professionals (YHC doctors and nurses) from both program regions and comprises of qualitative interviews (partly structured, partly in-depth), quantitative questionnaires and quantitative data regarding program uptake (e.g. the percentage of YHC professionals attending the skills training). The qualitative interviews will be conducted taking into account data saturation and will be audio-recorded with an Olympus voice recorder.

### Data management

The secured website for study registration and informed consent is hosted on the Maastricht University server and managed by the Data and Information Management Centre MEMIC Maastricht University. The personal participant data is stored separately from the study data in the secure Ldot Research Data and Workflow Management System from MEMIC Maastricht University. The sleep diary data is collected with a secure web-based sleep diary from MEMIC Maastricht University and stored in a certified Oracle research database. The certified Castor EDC platform is used for the digital questionnaires and storage of the questionnaire data. To promote retention and complete follow-up, the Ldot Management System assesses at each assessment timepoint whether the participant has filled in the study questionnaire and diary. In case a participant is almost overdue with data entry, a reminder e-mail or text message is sent to the participant, or a phone call is conducted to promote complete follow-up. Participants who fill in the sleep diary and questionnaires on paper, send their anonymous answers to the research team via post. Hereafter, the paper data will be entered in the Castor EDC or Oracle database by the researcher. The original paper documents are safely stored at Maastricht University. All used data management systems are General Data Protection Regulation (GDPR) compliant [66]. Only the research team and involved data management team from MEMIC Maastricht University have access to the study data. To ensure data quality, prior to analysis, all data will be checked by the researcher and will be cleaned to correct for extreme outliers, errors and duplicates.

### Data analysis

Continuous variables will be described in terms of means and standard deviations, while categorical data will be described using percentages and frequencies. Possible demographic differences between the program group and control group will be analysed using independent samples T-tests for continuous outcome variables and Pearson chi-square tests for categorical variables. The primary outcome ‘frequency of nighttime awakenings’ will be analysed by comparing the program group with the control group using a linear mixed model to account for potential confounders or relevant covariates, as well as possible clustering effects at the level of YHC teams, with T3 being the main timepoint of focus of the analysis. In case no substantial clustering effects are found, alternative approaches will be used to analyse the data at T3 if appropriate (e.g. linear regression or a one-sided independent samples T-test).

When appropriate, relevant covariates will be included into the analysis, such as feeding problems and major life events (e.g. parental divorce or illness at the moment of assessment), within a multiple regression analysis framework. In addition to the main analysis, further exploratory analyses will be performed. These include: effectiveness analyses at other assessment times, a repeated measurements analysis to identify changes between groups over the follow-up and analysis of program effects on secondary outcome measures, using the same approach as for the primary outcome in case of continuous variables and logistic regression or chi-square tests in case of categorical variables. All analyses will be performed in IBM SPSS Statistics 27 and/or R. Regarding the process evaluation, quantitative data will be analysed using descriptive statistics. The data of the highly structured part of the qualitative interviews will be reported in frequencies and percentages. The data of the in-depth part of the qualitative interviews will be transcribed verbatim and used as input for the iterative co-creation process and to provide context to the data from the highly structured part.

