**Methods:**

The program was developed based on co-creation with parents and Youth Health Care professionals, evidence-based behaviour change theories and sleep health promotion methods. Program effectiveness is investigated with a quasi-experimental study design comparing the program group with the care as usual control group. Participants consist of parents of 0-2-year-old children. Primary outcome is infant sleep quality at the age of 10 weeks and 6, 9, 14 and 24 months, measured with a sleep diary. The primary data analysis focuses on night awakenings at 9 months. Secondary outcomes focus on parental behaviour regarding infant sleep, related behavioural determinants and parental satisfaction with Youth Health Care sleep advice. Program effectiveness is analysed using a linear mixed-model in case of data clustering, and an independent samples T-test or linear regression in case no substantial clustering effects are found. A mixed methods process evaluation is performed with parents and Youth Health Care professionals, assessing program reach, adoption, implementation, maintenance and working mechanisms.

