### Study setting

This study takes place in the Dutch YHC setting for children aged 0–4 years. In the Netherlands, YHC is a nation-wide service providing preventative care for children aged 0–18 years and includes vaccinations, monitoring of infant growth and consultations for parents regarding infant development, health and parenting [51, 52]. It is available for all parents in the Netherlands, reaches up to 95% of young children and offers frequent consultations in the infant’s first four years of life, with on average nine consultations in the first year [40, 51, 52]. YHC is organised in regions, with parents receiving preventative care from the YHC centre of the region the infant is registered in. The program of this study is developed and implemented in two YHC regions (program region 1 and program region 2) in the South of the Netherlands. Program allocation was not random, for the program regions were chosen because of practical reasons and willingness to develop and implement a program in their organisation. The care as usual control group is formed by all YHC regions in the Netherlands that were not exposed to the program nor any of the program elements and provided usual care to parents. In the Netherlands, all YHC regions should adhere to the Dutch YHC infant sleep guidelines and the Dutch National Professional Framework for their infant sleep care [51, 53, 54]. Therefore, although there may be some regional variations in how these guidelines are applied, the standard of infant sleep care is expected to be similar across regions in the control group. Researchers, parents and YHC professionals were not blinded to the program.

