Regarding the study design, a strength is that in addition to the main reference timepoint at nine months, both short-term and long-term effects are investigated, due to having five measurement moments, starting at the age of 10 weeks and continuing until the child is two years old. Furthermore, not only infant sleep outcomes, but also intermediary and parental outcomes are assessed, which increases the studies’ sensitivity to find effects and aids in exploring factors that could be related to changes in infant sleep [49, 70]. When evaluating programs in real life settings such as YHC, it is also important to gain insight in program reach, adoption, implementation, maintenance and possible working mechanisms [71, 72]. Therefore, a thorough program evaluation is performed by combining a quasi-experimental effect evaluation with a mixed methods process evaluation [49, 71–73].

This study also has some limitations. One limitation may be that the study relies on subjective parental self-report using a sleep diary for the assessment of infant sleep. However, for this study, self-report measures were considered to be the most suitable option, for they are easy to administer, provide real-time insight in infant sleep and are considered less burdensome for the infant and more acceptable for parents in comparison with wearable sleep monitoring devices [74–76].

Another limitation may be the use of a quasi-experimental post-test only design, which may lower the study’s internal validity. However, for evaluation of complex, practice-based, population-level programs, it is necessary to find the right balance between internal validity and external validity [49, 70, 72, 77]. In the YHC context randomization is difficult, for being a program region requires quite some investment from local professionals, which is not possible in all YHC regions at all times. A post-test only design was chosen because in a study with newborn children, a pre-test measurement cannot be performed in the same child. Hence a quasi-experimental, post-test only study design was determined to be the most suitable design for this study, having the best balance between internal and external validity.

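### The primary 9-month comparison may become an unadjusted t-test when clustering looks small, although clustering says nothing about confounding between non-randomly chosen regions

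*Protocol article*

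**What the plan says.** The Data analysis section of the protocol article compares program and control on the frequency of night awakenings "using a linear mixed model to account for potential confounders or relevant covariates, as well as possible clustering effects at the level of YHC teams"; the main timepoint is T3. It then adds: "In case no substantial clustering effects are found, alternative approaches will be used to analyse the data at T3 if appropriate". The examples given are "e.g. linear regression or a one-sided independent samples T-test". The abstract repeats the rule with the t-test first: "an independent samples T-test or linear regression in case no substantial clustering effects are found".

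The next paragraph of Data analysis allows covariates into the analysis, where judged appropriate, within a multiple regression framework. Its examples are feeding problems and major life events. Demographic differences between the groups are to be tested, but no consequence for the primary model is stated.

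On the design, Study setting says: "Program allocation was not random, for the program regions were chosen because of practical reasons and willingness". The Discussion concedes: "Another limitation may be the use of a quasi-experimental post-test only design, which may lower the study’s internal validity".

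**The concern.** The condition for leaving the mixed model does not match what may be lost. Correlation among infants of the same team affects the standard error. Confounding affects the estimate itself, because parents and infants in two willing southern regions may differ from those elsewhere. A team correlation near zero is compatible with large differences between the two arms.

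The protocol itself gives a reason to expect trouble. Its Background says that infants of lower socioeconomic position sleep less and have more sleep problems, and socioeconomic position can differ by region. Since the design is post-test only, background characteristics are the main available means of making the groups comparable.

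At stake is whether the headline result is an adjusted estimate or a crude regional difference. Under the stated rule, that can be settled by a feature of the data that has no bearing on it.

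**Working it through.** **1. The plan's own figures (Participants section).** Inputs: d = 0.3, one-sided alpha 0.05, power 0.80, dropout 9%, intra-cluster correlation (ICC) 0.02, average cluster size 4.
- Exact noncentral-t calculation: 139 per group gives power 0.802, so 2 × 139 = 278.
- Dropout: 278 / 0.91 = 305.5, rounded up to 306.
- Design effect: 1 + (4 − 1) × 0.02 = 1.06, and 306 × 1.06 = 324.4, stated as 324 (162 per group).

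All three stated totals reproduce. There is no arithmetic error.

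**2. What each permitted T3 analysis does.**

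| Analysis | Handles team clustering | Can adjust for confounders |
|---|---|---|
| Linear mixed model | yes | yes |
| Linear regression | no | yes |
| Independent samples t-test | no | no |

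Moving from the first row to the second gives up only what the trigger is about. Moving to the third also gives up adjustment, for which the trigger provides no reason.

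**3. How much is lost by ignoring the clustering itself?** At the planned ICC and cluster size the one-sided error is 1 − Φ(1.645 / √1.06) = 1 − Φ(1.598) = 0.055, against 0.050. This is minor. The possible harm lies in lost adjustment.

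**4. How likely is the fallback?** The protocol names no test, so this step assumes an F-test for team effects within arms and equal teams of 4. Number of teams: 324 / 4 = 81 at recruitment, or 324 × 0.91 = 295 evaluable infants, 295 / 4 ≈ 74 teams.
- Ratio of expected mean squares: [1 + 3 × 0.02] / (1 − 0.02) = 1.06 / 0.98 = 1.082.
- 81 teams (79 and 243 df): the 5% critical value is 1.335; P(F > 1.335 / 1.082) = 0.115.
- 74 teams (72 and 222 df): the 5% critical value is 1.353; P(F > 1.353 / 1.082) = 0.111.
- At a 10% level the two figures are 0.200 and 0.195.
- With a true ICC of 0.05 and a 5% level they are 0.28 and 0.27.

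**5. Illustration of scale.** The documents give no size for confounding. Assume a bias b, in SD units, that adjustment would have removed. With 139 per group the standard error is √(2/139) = 0.120 SD. With no true effect, the one-sided rejection rate is 1 − Φ(1.645 − b / 0.120).

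| b (SD) | Share of planned d = 0.3 | b / SE | False-positive rate |
|---|---|---|---|
| 0 | 0% | 0 | 5% |
| 0.06 | 20% | 0.50 | 12.6% |
| 0.10 | 33% | 0.83 | 20.9% |
| 0.15 | 50% | 1.25 | 34.7% |

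Bias against the program lowers this rate (b = −0.10 gives 0.7%) but costs power. If the true effect is 0.3, a bias of −0.06 leaves an apparent effect of 0.24 and power of 64%; a bias of −0.15 leaves 0.15 and power of 35%. The planned power is 80%.

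**The case against.** The strongest reply is that reaching the fallback is not the same as losing adjustment. Data analysis lists linear regression before the t-test, qualifies the switch itself, and foresees covariates in a multiple regression framework. A sympathetic reading is that the team effect is dropped, regression is used, covariates enter where needed, and the t-test serves only if nothing needs adjusting. This stands in part: a reader might infer that the switch removes all confounder adjustment, and the text does not support that. But the qualifications are discretionary and do not exclude the t-test, which the abstract names first.

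A reader might also infer that the fallback will be used about nine times in ten. That follows only under the 5% F-test assumed above. The protocol speaks of substantial clustering, which could equally mean a size of ICC or design effect. Even under that test, the figure is the chance of reaching the fallback, not of reporting an unadjusted result.

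The bias figures are open to a third objection. They treat the whole bias as removable, whereas adjustment for measured characteristics in a post-test-only study may remove only part of it. Only that part can be charged to the switch, and its size is unknown.

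Finally, the missing threshold for substantial clustering and the missing list of covariates are details that an article may leave to the analysis plan. They are not the point here. The naming of an unadjusted test as a permitted primary analysis is stated text.

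**Conclusion.** The point holds as a permission that should not be there. The Data analysis section and the abstract both allow the primary T3 comparison to move from a confounder-adjusted model to a crude t-test, on a criterion unrelated to confounding, in a comparison between regions that were not randomly allocated. Loss of adjustment is possible, not certain, because linear regression is the other listed route.

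The mismatch between trigger and consequence follows from the wording alone and needs no assumption. The figure of 11 to 12% for detecting the planned clustering depends on the assumed 5% F-test and equal teams of 4. It shows that the fallback could well be the route taken. The rise from 5% to about 13 to 35% depends on an assumed, removable bias of 0.06 to 0.15 SD favouring the program. It shows scale only and is not a forecast for this trial.

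**What to change.** - Remove the independent samples t-test as a possible primary analysis at T3.
- State that negligible team clustering leads at most to dropping the random team effect, with the same covariates kept in a linear regression. Simply retaining the random effect is equally acceptable: if its variance is estimated as zero, the model reduces to that regression.
- Choose the covariates before outcome data are seen, from background characteristics already collected that the program cannot have affected, such as parental education, employment, ethnicity and birth order. Avoid current feeding mode: the demographics questionnaire may be completed until the infant is 14 weeks old, when contact with the service may already have begun.
- Report the crude difference as descriptive only.
- Bring the abstract into line.

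The cost is wording in the protocol and analysis plan. No new data are needed and the sample size stays at 324. Retaining the random effect may widen the interval slightly.

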## Background

Sleep problems are common amongst infants. According to international studies, approximately 20–30% of infants and toddlers experience sleep problems such as delayed sleep onset, frequent nighttime awakenings and early awakenings [1–4]. Moreover, many parents report having difficulties with managing their infant’s sleep, even when their child’s sleep appears to be normal [5–7]. Since infant sleep differs significantly from adult sleep, often includes night awakenings and is subject to many changes during infant development, it can be a challenge for parents to adequately manage infant sleep behaviour [2, 8]. Consequently, infant sleep is an issue parents frequently seek help for from healthcare professionals [6, 9–11].

When infant sleep problems arise, they can seriously impede the child’s development by its various negative outcomes such as behavioural and cognitive problems, social-emotional problems and a higher risk on overweight and obesity [12–15]. Furthermore, sleep problems at an early age can persist into childhood and may become chronic [3, 16–18]. Infant sleep problems can have serious consequences for parents as well. They have been associated with parental depression, increased parental stress, reduced parental sleep quality and quantity and worse overall parental health [1, 19–22]. Interestingly, research indicates a reciprocal relationship between infant sleep and parenting effectiveness [5, 10, 23]. Due to this reciprocity, infant sleep problems may result in a vicious circle wherein parental fatigue reduces parent’s ability to adequately manage their child’s sleep, leading to a continuation of the sleep problem [5, 10, 23].

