Many factors influence infant sleep and many factors determine whether or not infant sleep becomes problematic. To describe these factors, Sadeh and Anders developed the transactional systems model of sleep-wake regulation in infants [23, 24]. This model stresses the importance of the direct relationship between infant sleep and parent-infant interactions [23, 24]. Behaviours such as reduced parental limit setting as well as a high level of assistance in the child falling asleep, such as soothing the child to sleep, are related to the development of sleeping problems in young children. Such behaviours may interfere with the development of self-regulation skills in the child, which are necessary for the child to be able to self-soothe and fall asleep independently [5, 10, 23, 24]. Infant sleep is also subject to significant income-related health disparities: children with a lower Socioeconomic Position (SEP) generally have a shorter sleep duration, more sleep problems and poorer sleep habits in comparison with children of higher SEP [25–28]. Consequently, addressing infant sleep and related parent-infant interactions seems to be a crucial step in promoting healthy infant development, providing support for parents and reducing health disparities.

Various sleep health promotion programs that target these parent-infant interactions in healthy infant populations have been developed and evaluated [1, 29–33]. Such programs often comprise of educational or behavioural elements or a combination of the two. In general, the purpose of educational programs is to prevent sleep problems by providing parents with information about normal sleep and crying patterns, infant cues and strategies to promote infant self-settling (e.g. putting the child to bed drowsy but awake), but can also include education on behavioural strategies [30, 32]. Behavioural programs often comprise of elements such as a consistent sleep schedule, bedtime routines and sleep management techniques focused on removing the reinforcement of the problematic sleep behaviour, by using controlled crying strategies [1, 29–33].

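### In a non-randomised comparison, the primary analysis names no pre-exposure confounder, offers only possibly post-exposure covariates as examples, and allows an unadjusted t-test

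*Protocol article*

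**What the plan says.** All references are to the protocol article.

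- **Allocation (Study setting):** "Program allocation was not random, for the program regions were chosen because of practical reasons and willingness to develop and implement a program". The comparison group is every Dutch region not exposed to the program.
- **Design (Discussion):** "Another limitation may be the use of a quasi-experimental post-test only design, which may lower the study’s internal validity". No pre-program outcome is available to adjust for.
- **Primary model (Data analysis):** a linear mixed model at T3, said to handle potential confounders, relevant covariates and clustering by care team. No confounder is named.
- **Covariates (Data analysis):** "When appropriate, relevant covariates will be included into the analysis", with the examples "such as feeding problems and major life events (e.g. parental divorce or illness at the moment of assessment").
- **Fallback (Data analysis, and in similar terms the Abstract):** if clustering is not substantial, linear regression or an independent samples t-test, one-sided in Data analysis.
- **Demographics collected (Demographic information), before the infant is 14 weeks old:** parental age, family composition, education, employment and ethnicity, and for the infant sex, "birth order position, ethnicity and whether the infant primarily receives breastfeeding, formula feeding or a combination of the two".
- **Stated use of the demographics (Data analysis):** "Possible demographic differences between the program group and control group will be analysed using independent samples T-tests", with chi-square tests for categorical variables.
- **Prognostic background (Background):** "Infant sleep is also subject to significant income-related health disparities". On the consequences of infant sleep problems for parents: "They have been associated with parental depression, increased parental stress, reduced parental sleep quality and quantity and worse overall parental health".

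**The concern.** With no randomisation and no baseline outcome, the adjustment set is the main protection against confounding. The text goes wrong in three ways.

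1. The only explicit examples point to the wrong kind of variable. A life event or illness at T3 occurs after months of program exposure. Because the Background links infant sleep problems to parental stress and poorer parental health, parental illness at T3 may partly follow from the outcome. Feeding problems, if recorded late, could lie on the path from program to sleep. A model holding such variables fixed does not estimate the program's total effect.
2. The variables that precede exposure and could differ between regions are not named for the model. One of them, education as a marker of socioeconomic position, has support in the article's own Background.
3. The choice between an adjusted model and a plain t-test depends on clustering. Clustering affects the standard error; confounding affects the estimate. A negligible intra-cluster correlation is no reason to drop adjustment.

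An analyst following the stated text could therefore report a confounded estimate, an over-adjusted one, or a set of covariates settled after the data were seen.

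**Working it through.** **1. The plan's own figures.** Inputs from Participants: d = 0.3, one-sided alpha 0.05, power 0.80, dropout 9%, intra-cluster correlation 0.02, cluster size 4.
- The one-sided t-test needs 138.07, rounded up to 139 per group, so 278.
- 278 / (1 − 0.09) = 305.5, so 306.
- Design effect 1 + (4 − 1) × 0.02 = 1.06; 306 × 1.06 = 324.4, so 324 (162 per group).

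The stated sample size reproduces and is not in question.

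**2. What a demographic significance test can show.** Two-sided 5%, 162 per group, imbalance δ in SD units. Power ≈ Φ(δ√(162/2) − 1.96) = Φ(9δ − 1.96).

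| δ | 9δ − 1.96 | Power |
|---|---|---|
| 0.1 | −1.06 | about 15% |
| 0.2 | −0.16 | about 43% (0.434 by the t distribution, 0.436 by the normal) |
| 0.3 | 0.74 | 77% |

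With 139 per group the last two become 39% and 71%. A non-significant result is thus weak evidence of balance at 0.2 SD or below.

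**3. Bias from an omitted confounder.** Bias = imbalance (SD) × slope on awakenings (SD per SD). Both inputs are assumptions; the article gives neither.

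| Imbalance | Slope | Bias (SD) | Share of d = 0.3 |
|---|---|---|---|
| 0.2 | 0.2 | 0.04 | 13% |
| 0.2 | 0.3 | 0.06 | 20% |
| 0.3 | 0.3 | 0.09 | 30% |
| 0.5 | 0.3 | 0.15 | 50% |

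With 139 per group the standard error is √(2/139) ≈ 0.12. If there were no true effect and the bias favoured the program, the one-sided 5% error rate would be 1 − Φ(1.645 − 0.04/0.12) ≈ 10% at the low end and 1 − Φ(1.645 − 0.15/0.12) ≈ 35% at the high end. The bias could equally run against the program.

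**4. Adjusting for a consequence of T3 sleep.** If the covariate C follows from the outcome Y with within-group correlation r, the group coefficient is multiplied by (1 − r²) and its z-value by √(1 − r²). Start from z = 1.645 + 0.8416 = 2.4865 at 80% power.

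| r (assumed) | Effect retained | Power |
|---|---|---|
| 0.1 | 0.99 | Φ(2.474 − 1.645) ≈ 80% |
| 0.3 | 0.91 | Φ(2.372 − 1.645) ≈ 77% |
| 0.5 | 0.75 | Φ(2.153 − 1.645) ≈ 69% |

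**5. How large r could be.** A rare binary event cannot easily reach a high r. The difference in awakenings needed between families with and without the event is r / √(p(1 − p)) SD. At an assumed prevalence of 5%, r = 0.3 needs 0.3/0.218 ≈ 1.4 SD and r = 0.5 about 2.3 SD. At 10% they need 1.0 and 1.7 SD. For events such as divorce, the lower rows of the table in step 4 are therefore implausible, and shrinkage near 1% is the more realistic order.

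**The case against.** The strongest reply is that the article does provide for confounders. It assigns that task to the mixed model immediately after describing the demographic tests, and nowhere says that a non-significant test keeps a variable out. The named covariates are only examples, conditional on being appropriate, and a full list may stand in an analysis plan that is not shown.

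This disposes of three tempting inferences:

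- **That collected baseline variables will only be significance-tested.** The documents do not support this. Testing is their only explicit use, but the provision for confounders may cover them.
- **That both example covariates are measured at the assessment.** That timing is attached to the life-event examples alone. Feeding problems have no date.
- **That these covariates result from the program or the infant's sleep.** The Background reports associations with parental stress and health, not with divorce. No section says the program changes feeding problems. Illness is not clearly confined to the parent; an acute infant illness could be an outside cause of waking, and adjusting for it could improve precision.

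It is also fair that the shrinkage in step 4 rests on assumed correlations, and that 0.3 or 0.5 is probably high.

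What the reply does not answer is the text that is stated. The only examples given are after exposure or undated, an unadjusted t-test is expressly allowed, and its trigger is unrelated to confounding. Those are choices in the article, not details left out of it.

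**Conclusion.** The point holds in limited form. The article does not rule out adjustment for baseline confounders, but it commits to none, its examples are poor guides for a total-effect estimate, and its fallback can remove adjustment altogether in a design that depends on it.

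The larger risk is uncorrected confounding: 0.04 to 0.15 SD, or 13% to 50% of the planned effect, under assumed imbalances of 0.2 to 0.5 SD and slopes of 0.2 to 0.3. Over-adjustment is the smaller risk: 1% at r = 0.1 and 9% at r = 0.3, if the covariate is a consequence of T3 sleep at all. The article gives no value for any of these inputs, so the figures show a range and not an expected bias. The point should be settled before analysis; it does not invalidate the study.

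**What to change.** 1. Fix the adjustment set for the primary T3 model from variables already collected that precede exposure: at least parental education (as the marker of socioeconomic position), ethnicity, family composition and birth order. Parental age and infant sex are optional additions. Include the set regardless of any between-group test.
2. If clustering proves negligible, fall back to linear regression with the same set. Remove the unadjusted t-test as a primary analysis.
3. Move life events or illness at assessment, and feeding problems arising after exposure began, to a labelled sensitivity analysis. Treat early feeding mode as a sensitivity covariate too, since it may be recorded up to 14 weeks, after contact with the program may have started.
4. State that the demographic comparisons are descriptive and do not select covariates. Standardised differences would serve this better than p-values.

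Cost: a change of wording in the analysis plan, a few degrees of freedom and one extra sensitivity analysis. No new data are needed for the primary set, and N = 324 stands.
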